## Abstract

**Background:**

The challenges imposed by ageing populations will confront health care systems in the years to come. Hospital owners are concerned about the increasing number of acute admissions of older citizens and preventive measures such as integrated care models have been introduced in primary care. Yet, acute admission can be appropriate and lifesaving, but may also in itself lead to adverse health outcome, such as patient anxiety, functional loss and hospital-acquired infections. Timely identification of older citizens at increased risk of acute admission is therefore needed.

We present the protocol for the PATINA study, which aims at assessing the effect of the ‘PATINA algorithm and decision support tool’, designed to alert community nurses of older citizens showing subtle signs of declining health and at increased risk of acute admission. This paper describes the methods, design and intervention of the study.

**Methods:**

We use a stepped-wedge cluster randomized controlled trial (SW-RCT). The PATINA algorithm and decision support tool will be implemented in 20 individual area home care teams across three Danish municipalities (Kerteminde, Odense and Svendborg). The study population includes all home care receiving community-dwelling citizens aged 65 years and above (around 6500 citizens). An algorithm based on home care use triggers an alert based on relative increase in home care use. Community nurses will use the decision support tool to systematically assess health related changes for citizens with increased risk of acute hospital admission.

The primary outcome is acute admission. Secondary outcomes are readmissions, preventable admissions, death, and costs of health care utilization. Barriers and facilitators for community nurse’s acceptance and use of the algorithm will be explored too.

**Discussion:**

This ‘PATINA algorithm and decision support tool’ is expected to positively influence the care for older community-dwelling citizens, by improving nurses’ awareness of citizens at increased risk, and by supporting their clinical decision-making. This may increase preventive measures in primary care and reduce use of secondary health care. Further, the study will increase our knowledge of barriers and facilitators to implementing algorithms and decision support in a community care setup.

**Trial registration:**

ClinicalTrials.gov, identifier: NCT04398797. Registered 13 May 2020.

## Background

The challenges imposed by demographic changes will confront health care systems in the years to come [1]. It is a global concern that even highly effective health care systems will struggle with meeting the demands of ageing populations [2], as higher age is associated with multimorbidity, health deterioration with functional decline, and subsequent increased utilization of health care services [3–6].

In older citizens acute hospitalization can be highly necessary and lifesaving, but may also lead to adverse consequences, such as hospital-acquired infections, anxiety and distress, poorer functional health, and death [3, 7–10]. Prevention of acute admission is therefore exceptionally important in higher age groups, but requires timely detection of disease symptoms, functional and mental deterioration and health care interventions. However, early recognition of disease is hampered by diagnostic challenges following older citizens’ higher prevalence of multimorbidity, polypharmacy, functional impairment, and social issues, which altogether yield complex interactions and increases the risk of mismanagement [11]. In addition, atypical presentation of symptoms may delay timely diagnosis, which is why novel predictive tools are needed for timely recognition of older citizens at increased risk of acute disease and subsequent acute hospitalization [12].

Prediction models using data from electronic health records to identify those in the highest risk of acute hospitalization have been increasingly studied. A systematic review from 2014 identified 27 prediction models for acute admissions. However, only half of the models were targeted older citizens, and in addition, the predictive models in general required large administrative or clinical data sets, which were analyzed retrospectively [13]. Most models are based on data from electronic hospital records and many have been found effective in predicting risk of acute admissions [13–19]. Only a few studies have focused on prediction models solely based on home care data [20], and very few studies have implemented and tested a prediction model in practice, mainly due to ethical and economic considerations [21], barriers among professionals, such as trust in the technology [22], and the fact that data on health and care is registered primarily for the use and support for health professionals, not for input to algorithms [23]. Thus, datasets are more often designed for retrospective analysis than for prospective use [24].

In a tax-funded (Beveridgian) health care system free of charge for health care receivers utilization of health and home care services mirrors older citizen’s overall health [25]. An increased need of health care may be the first sign of emerging acute disease. In an earlier retrospective study, we found a significant increase in municipal home care service (hours/week) over a 12-month period prior to acute hospitalization [3]. Based on this finding we have developed the Prevention of AcuTe admIssioN Algorithm (PATINA), a novel predictive model that analyzes administrative data on home care utilization and yields a warning to community nurses (hereafter referred to as nurses) about citizens at increased risk of acute hospitalization. Further, to assist nurses in their assessment of citizens identified by the algorithm as being ‘at risk’, a decision support tool has been developed. The intervention is presented in the method section.

The primary objective of the PATINA project is to implement and evaluate the combined effect of the ‘PATINA algorithm and the decision support tool’ on the prevention of acute hospital admissions of older community-dwelling citizens [3]. Further, we will evaluate the effects on citizens utilization of health care service in the primary and secondary health care sector and estimate costs. A second objective is to investigate nurses’ role in achieving the desired effects of the implementation, by linking employees’ motivation and attitudes toward the ‘PATINA algorithm and the decision support tool’ to the primary and secondary outcome of the study.

In this paper, we present the study protocol for the PATINA project, where we use a stepped-wedge randomized controlled trial, explaining the methods, design and intervention of the study. The study protocol (version 1.2, 13 May 2020) follows the SPIRIT statement [26] and has been adapted to suit the format of an article.

## Methods/design

### Study design

The study is designed as a multicenter randomized controlled trial using a stepped-wedge cluster design (Fig. 1) to implement and test the ‘PATINA algorithm and decision support tool’ in three Danish municipalities. Three stages will sequentially be rolled-out across the area home care teams in the three municipalities (described later); usual care exposure; intervention implementation and intervention exposure, followed by a one month and three-month post intervention follow-up. The timing of the one-way crossover from usual care to intervention exposure is randomly allocated during the intervention period (June 1, 2020 – May 31, 2021).

**Fig. 1 Fig1:**
[figure not shown]
The PATINA study stepped-wedge design in three municipalities with three (Kerteminde), seven (Svendborg) and 10 (Odense) area home care teams. With a scheduled randomized inclusion of an area home care team every twelfth week in Kerteminde, every sixth week in Svendborg and every fourth week in Odense Municipality. With a one- and three-month follow-up

#### Setting and study population

Denmark has 5,8 million inhabitants (2020), of which 264.000 are 80 years or older, a number forecasted to increase to 670.000 in 2057 [27]. Like most Nordic countries the Danish public welfare system is tax funded and builds on a societal consensus that the public sector is responsible for providing good and equal health and social care [28, 29]. Health care, i.e. hospital treatment, consultations with a primary care physician or specialist physician, and home care, is universal and free of charge at the point of utilization [30]. Health care services are provided by five regions, who are responsible for operating and funding hospitals and financing primary care physicians and specialist physicians, while the 98 municipalities are responsible for providing home care and social care, care in care homes, nursing care, training and rehabilitation, health promotion and more [30]. Municipalities strive to care for older citizens in their own home as long as possible. Municipal health care services are allocated based on the citizen’s functional level and ability of self-care and may be adjusted following changes in an individual’s self-care ability. Home care, nursing care and rehabilitation services are all delivered by the municipal area home care teams, which are organized in teams covering specified geographical areas. Unlike many other countries nursing care in the community is thus delivered by the municipalities and not by a national health service [30].

The trial is carried out in three Danish municipalities of different sizes, populations, and organizational characteristics: Kerteminde as the smaller, Svendborg as the medium sized and Odense as the larger municipality (see description in Table 1). In each municipality we include area home care teams (20 in total for all three municipalities), that primarily have a focus on delivering health care services to community dwelling older citizens. Two additional area home care teams in Odense Municipality have already been excluded as their primary focus is younger citizens with mental disorders, not older citizens.

**Table 1 Tab1:** Characteristics of the three intervention municipalities in the PATINA study [27]. OADR: Old Age Dependency Ration (OADR), ratio between the number of citizens aged 65+ years and the number of persons in the working age 15–64

	Kerteminde	Svendborg	Odense
Size, km^2^	207	417	305
Population, N	23,833	58,355	205,881
Population above 65 years of age, n	6142	14,206	35,811
Population above 80 years of age, n	1590	3407	9012
Old age dependency ration (OADR), 15–64/65+ years	0.43	0.39	0.25
Organizational characteristics of area home care teams	Geographical unites	Geographical unites	Unites organized by mental and somatic disease characteristics and geography
Number of area home care teams (included in the study)	3 (3)	7 (7)	12 (10)

The study population will include all community-dwelling citizens above 65 years of age, who receive home care in Odense, Kerteminde and Svendborg Municipalities.

#### Intervention

The intervention is the ‘PATINA algorithm and the decision support tool’, which systematically guides nurses in their overall health assessment of citizens flagged by the algorithm.

#### PATINA algorithm

The algorithm monitors and analyzes community-dwelling older citizens’ use of municipal home and nursing care with almost real time data (one-week delay). It uses individual administrative data on assigned amount of time (minutes per week) for home care, practical (domestic) help, training/rehabilitation, and nursing care delivered to each citizen.

In each of the three municipalities, a weekly data set with information on health care use during the past week is fed into three separate secure databases via a front-end upload module. Data is then analyzed by the algorithm by comparing home care utilization the last month to a prior period of six months. The algorithm then produces a list of citizens that have triggered the threshold configured for the algorithm. A graph visualizing each citizens utilization of personal care, practical help, training/rehabilitation and nursing care during the last six months is also produced, see Fig. 2.

**Fig. 2 Fig2:**
[figure not shown]
Graph from the PATINA algorithm visualizing a citizen’s utilization of home care (practical help and personnel care), nursing, training and total help

In the intervention phase, nurses in the included area home care teams receive the list of citizens that have surpassed the threshold. These are considered to be at increased risk of adverse health outcomes and subsequently of acute hospitalization. The list also provides graphs visualizing each citizens’ health service utilization. Simultaneously, the algorithm sends the information to a research database setup in Redcap [31, 32], which then forwards a unique link for each citizen to an allocated community nurse. The link gives the nurse access to the ‘PATINA decision support tool’. The tool is designed as a questionnaire, which is covered and filled-in by the nurse.

#### PATINA decision support tool

The PATINA decision support tool is designed to nudge nurses to reflect upon more recent notifications in the electronic care records regarding changes in health and need of care. Such changes may be subtle signs of health deterioration, and not just ageing processes. Additionally, the ‘PATINA decision tool’ includes validated health assessment scales and information on risk factors of acute disease, such as functional level (Barthel-20) [33], frailty (Clinical Frailty Scale) [34, 35], Brief Geriatric Assessment [36], medications, falls tendency, weight, mental state, dehydration, and more. Further, the tool supports and covers areas of health care, which nurses in Denmark are obligated to assess regularly, e.g. assessment of citizens general state of health [37].

Nurses complete the decision support workflow by reviewing information in the citizen’s electronic care record and apply their knowledge about the citizen from their daily work. After assessing a ‘citizen at risk’ using the decision support tool, the data is sent to the research database and a PDF file containing the assessment is automatically forwarded to the nurse via email. The PDF file is then saved on the citizen’s electronic health record for later use by the nurse and other colleagues, as well as for reference.

Data from the citizen can trigger the algorithm’s alarm for several weeks in a row. The first time a citizen appears on the list the nurse must assess the citizen’s current health and functional situation using the PATINA decision support tool. When a citizen continues to be on the list, the nurse compares the citizens actual health care situation with the latest ‘PATINA decision tool assessment’, thereby judging whether the citizen’s situation has worsened, and further action is needed. In this case the citizen is assessed once more using the decision tool and a PDF file is saved as a new reference point.

The IT ecosystem and data flow of the project are visualized in Fig. 3. A more detailed description of how the algorithm has been developed, IT infrastructure and security, and how the threshold was configured, will be presented later in a separate paper.

**Fig. 3 Fig3:**
[figure not shown]
The IT-ecosystem and dataflow in the PATINA algorithm and decision support tool. The figure was created using draw.io (open-source freeware)

### Study procedures

#### Randomization and implementation

The stepped-wedge design allows all 20 area home care teams across the three municipalities to receive the intervention, but at different time points according to randomization. Following the time schedule, a new area home care team is included in Kerteminde Municipality approximately every 12 weeks, in Svendborg Municipality every six weeks, and in Odense Municipality every four weeks (Fig. 1). The computer-generated stepwise randomization is carried out by a statistician from Open Patient data Explorative Network (OPEN), Odense University Hospital, Region of Southern Denmark.

All three municipalities are made aware of the randomization procedure prior to study start. However, the starting date for the intervention exposure will not be announced until four weeks prior to implementation start.

In this study it is not possible to blind neither nurses or other health care professionals, nor the management in each municipality. However, nurses and the management are instructed only to talk about the project with coworkers within their own area home care team, and not with colleagues in other teams.

#### Study outcome

The primary outcome of the study is acute hospital admission. Secondary outcomes cover readmission, preventable admission, contacts to outpatient clinics, death as well as changes and costs in health care utilization. Further, we will investigate barriers and facilitators for community nurse’s acceptance and use of the algorithm using data gathered in a three-wave survey sent to nurses in the individual area home care teams, which will be integrated in the SW-RCT design. The study outcomes and outcome measures are presented in Table 2.

**Table 2 Tab2:** Project outcomes and outcome measures in the PATINA study

	Outcome	Outcome measure
***Primary outcome***		
Outcome 1	Acute admission	Proportion of acute hospital admissions after being identified at risk by the algorithm

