***Secondary outcomes***		
Outcome 2	Preventable admission	Preventable admission after being identified at risk by the algorithm
Outcome 3	Readmission (30-days)	Readmission to a Danish hospital within 30 days from a hospital discharge
Outcome 4	Outpatient contacts	Proportion of contacts to outpatient clinics after being identified at risk by the algorithm
Outcome 5	Primary care physicians contacted	Contacts to a primary care physician after being identified at risk by the algorithm
Outcome 6	Death (90-days)	Proportion of diseased citizens identified at risk by the algorithm within 90 days

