### Data analyses

#### Sample size and statistical power

The three municipalities, Odense, Svendborg and Kerteminde, provide access to data on all citizens age 65+ and over, who receive home or nursing care, yielding an expected study population between 5.500–6.000 individuals.

We have calculated the power of the study using an assumption of a one-sided significance level of 0.05 and equal sample size between the intervention and control group. It has not been possible to identify previous studies investigating the effects of monitoring utilization of home care combined with an intervention to prevent acute admission. Thus, we use a conservative estimate of 10% difference in number of acute admissions between the intervention (10.8%) and control group (12%) [38]. On the basis of these assumptions the power in each of the three municipalities seems rather modest (Odense β = 0.15, Svendborg β = 0.12, Kerteminde β = 0.1). Across the three municipalities the power is somewhat greater, the β will at least be 0.22 depending on the timing.

The power calculation was carried out using STATA 16 and the command” .steppedwedge”, as described by Hemming and Taljaard [39].

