#### Analysis of primary and secondary outcomes

Outcomes are shown in Table 2. The primary outcome, proportion of acute admission, will be analyzed using co-variance, repeated measure analysis and logistic regression. A key event is the switch from the usual care to intervention phase. We will treat the intervention regression coefficient as a slopes term to account for potential differences in intervention effects across area home care teams. The analyses will be adjusted for relevant confounders such as age, gender, co-morbidity, functional level and frailty.

For secondary outcomes (Table 2) 2, 3, 4, 5 and 6 we will use logistic regression to analyze occurrence of event. Citizens, who relocate to another municipality, move into a care home, or die during the study period will be excluded from the analyses. Models for acute admission will be used and the incidence of acute admission will be analyzed using logistic regression. The analysis will be adjusted for confounding factors such as age, gender and co-morbidity. We will stratify the analyses by municipalities and area home care teams to control for differences between these.

When analyzing readmission between the intervention and control group we will focus on both the 30-day readmission rate (outcome 3) and 90-day readmission rate (outcome 4). The index-admission will be defined as any admission to a Danish hospital during the study period. Citizens with multiple hospital admissions can have several index admissions but only one readmission per index admission.

Changes in citizens health service utilization (outcome 7, 8 and 9) will be evaluated in order to assess changes in costs of care and treatment in the primary and secondary health care sector. We will analyze the average cost per citizen, as well as analyses of the change in costs in primary and secondary health care. We will also analyze the costs of implementing the PATINA algorithm and decision support tool (outcome 10). This will be done by summing up the time spent on project related activities by both nurses and project coordinators in each municipality. The costs of implementing the algorithm will be reported as the total cost of the intervention with a 95% confidence interval.

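### The primary outcome leaves out death as a competing event, and excluding citizens who die weakens the one outcome that would show a shift from admission to death

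*Protocol article*

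**What the plan says.** Table 2 of the protocol article gives the primary outcome measure as "Proportion of acute hospital admissions after being identified at risk by the algorithm". It says nothing about a citizen who dies before any admission.

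The article does not treat admission as bad in itself. The abstract says "acute admission can be appropriate and lifesaving, but may also in itself lead to adverse health outcome", and the Background section says "In older citizens acute hospitalization can be highly necessary and lifesaving".

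Death appears as secondary Outcome 6: "Proportion of diseased citizens identified at risk by the algorithm within 90 days" (the third word evidently means deceased).

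Two statements bear on how citizens who die are analysed:

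- The section on statistical analyses promises intention to treat, with all eligible patients who have outcome data.
- The section on analysis of primary and secondary outcomes, in the paragraph on Outcomes 2 to 6, says "Citizens, who relocate to another municipality, move into a care home, or die during the study period will be excluded from the analyses". The next sentence reads "Models for acute admission will be used and the incidence of acute admission will be analyzed using logistic regression".

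**The concern.** The trial will be judged by whether fewer flagged citizens are acutely admitted. Death without admission precludes the event, so it competes with the outcome. A lower proportion can arise because deterioration was caught early, or because citizens who would have been admitted died at home instead. The primary measure cannot tell these apart.

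The article itself supplies the reason to care, since it says admission may be lifesaving. It also says that nurses and management cannot be blinded (Randomization and implementation) and that municipalities have an economic reason to avoid unnecessary hospital use (Discussion). Neither statement shows that care would be withheld. Both are reasons to choose a set of outcomes that does not score prevention and withholding alike.

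At stake is what a positive primary result would mean. Mortality is the obvious cross-check, but the article does not link it to the reading of the primary result, and the exclusion rule takes deaths out of its analysis.

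**Working it through.** **Inputs from the article.** Acute admission of 12% under control and 10.8% under intervention (Sample size and statistical power). The planned effect reproduces: (12.0 − 10.8)/12.0 = 1.2/12.0 = 10% relative.

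**Assumptions.** The article gives no death rate, so these are illustrative.

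- Of every 1,000 flagged citizens, *s* move from admission with survival to death without admission, with *s* = 6, 12 or 24. Nobody else changes.
- *b* citizens per 1,000 die without admission in both conditions, with *b* = 0, 30 or 60.
- All outcomes are counted over one common window.

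**Formulas, per 1,000 flagged citizens.**

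- Deaths kept as not admitted: control 120/1,000; intervention (120 − s)/1,000.
- Deaths excluded: control 120/(1,000 − b); intervention (120 − s)/(1,000 − b − s).
- Admission or death: control (120 + b)/1,000; intervention (120 − s + b + s)/1,000, which is the same number.

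**Results with b = 0** (control 12.0% throughout).

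| Shift s | Deaths kept | Deaths excluded | Admission or death |
|---|---|---|---|
| 6 | 114/1,000 = 11.4% (5.0% lower) | 114/994 = 11.47% (4.4% lower) | 12.0%, unchanged |
| 12 | 108/1,000 = 10.8% (10.0% lower) | 108/988 = 10.93% (8.9% lower) | 12.0%, unchanged |
| 24 | 96/1,000 = 9.6% (20.0% lower) | 96/976 = 9.84% (18.0% lower) | 12.0%, unchanged |

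**Sensitivity to background deaths.** With b = 60 and s = 12, exclusion gives 120/940 = 12.77% against 108/928 = 11.64%, or 8.8% lower, and the composite is 18.0% in both conditions. Across the values tried, background deaths move the relative figures by at most 0.1 percentage point.

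**A boundary case.** If the shifted citizens would have died in the study period even after admission, exclusion removes them from both conditions. Both proportions are then 108/988 = 10.93% and no false benefit appears. Under exclusion the problem is therefore confined to citizens whom admission would have saved, which is the harmful case. If deaths are kept, the fall to 10.8% appears either way.

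**What mortality would show.** With s = 12, deaths rise by 12 per 1,000, or 1.2 percentage points, if citizens who die are analysed. Outcome 6 would then reveal the shift, provided the deaths fall within 90 days of the flag. Under the exclusion rule these deaths leave the analysis. Outcome 6 is among the outcomes named in that paragraph, so read literally it has few or no deaths left to count. Any that remain would have to fall outside the study period.

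**The case against.** A reader might infer that the protocol scores an unadmitted death as a prevented admission, and that the primary comparison is therefore biased towards benefit. The article does not support either statement. It never says that such a death counts as not admitted. Its only written rule on death is exclusion, which takes the citizen out of numerator and denominator alike. That rule's reach is unclear: it stands in the secondary-outcomes paragraph, but the next sentence turns to acute admission. If it does not reach the primary outcome, the intention-to-treat statement makes retention as not admitted the natural reading, but that is an inference. A bias would also need an actual shift towards unadmitted death, and the described intervention is an alert with a structured health assessment. Nothing in it tells nurses to discourage admission.

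Three further points deserve weight:

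- The shift of 12 per 1,000 was chosen to match the planned effect and has no source in the article. This stands. The figures show what could be hidden, not what is likely.
- Outcome 2, preventable admission, gives some help: a fall in all admissions without a fall in preventable ones would be a warning. This stands in part, since Outcome 2 does not show whether the citizens concerned died.
- An interpretation rule is often left to the analysis plan, and only a condensed article is shown. That would excuse silence. It does not excuse a stated rule that conflicts with intention to treat and removes deaths from the analysis of a death outcome.

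**Conclusion.** The point holds as a weakness in how the outcomes are fixed, not as a demonstrated bias. A shift from admission to unadmitted death would lower the primary proportion under either handling of deaths. For an assumed 12 per 1,000, the fall is from 12.0% to 10.8% or 10.93%, which is all or most of the planned 10% relative effect, while admission-or-death does not move. Under exclusion this requires that the shifted citizens would have survived if admitted. The direction does not depend on the assumed background death rate, and the size scales with the assumed shift.

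The part that rests on the text alone is the weakened safeguard: 90-day death is a listed outcome, yet citizens who die during the study period are excluded from the analyses that include it. The trial remains feasible, and the change should be made before results are read.

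**What to change.** Keep acute admission as the primary outcome and make four changes.

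1. Delete death from the exclusion rule in the section on analysis of primary and secondary outcomes. State that citizens who die are retained in the analyses of Outcomes 1 and 6, in line with intention to treat.
2. Add a key secondary outcome: acute admission or death from any cause within 90 days of the flag, analysed with the primary model. Outcome 6 already uses the 90-day window.
3. Report any fall in admissions together with this composite and the 90-day mortality difference with its confidence interval.
4. Call a fall in admissions a benefit only if the composite also favours the intervention. A weaker condition, such as withholding the claim only when the composite worsens, would not be enough: in the worked example the composite stays flat. For the same reason the mortality difference must stand beside it, because the composite weighs an admission and a death equally.

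The cost is one more secondary analysis and a more cautious claim. No new source should be needed: admissions come from the National Patient Registry already linked under Data collection, and Outcome 6 already requires vital status.

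### The primary outcome starts at the flag but has no end and no rule for the team's crossover, so follow-up length and exposure are undefined for citizens flagged under usual care

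*Protocol article*

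**What the plan says.** All references are to the protocol article.

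- **Primary outcome (Table 2):** "Proportion of acute hospital admissions after being identified at risk by the algorithm". No time limit is attached.
- **Other outcomes in the same table:** readmission is "Readmission to a Danish hospital within 30 days from a hospital discharge", and death is "Proportion of diseased citizens identified at risk by the algorithm within 90 days".
- **Study design:** the roll-out from 1 June 2020 to 31 May 2021 is "followed by a one month and three-month post intervention follow-up". This follow-up comes after the intervention period. It is not tied to the flag or to the primary outcome.
- **Schedule (Fig. 1 legend):** "three (Kerteminde), seven (Svendborg) and 10 (Odense) area home care teams", with a new team entering "every twelfth week in Kerteminde, every sixth week in Svendborg and every fourth week in Odense Municipality".
- **Analysis:** the primary outcome is a proportion, to be analysed with covariance, repeated-measures and logistic methods. "A key event is the switch from the usual care to intervention phase". Statistical analyses adds that analysis follows the randomization schedule. Neither section says where to place an admission that comes after the switch in a citizen flagged before it.
- **Repeat flags (PATINA decision support tool):** a citizen may trigger the alarm in successive weeks, so the same person can be flagged in both phases.
- **Time (Discussion):** the authors commit to adjusting for clustering and for the confounding effect of time.

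**The concern.** Crossover is one-way and staggered, so control flags come early in the year and intervention flags late. A proportion that starts at the flag and has no end then raises two separate problems.

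1. **Unequal opportunity.** A citizen flagged early, usually under usual care, has longer to be admitted than one flagged late. A yes/no outcome will favour the intervention even if it does nothing.
2. **Mixed exposure.** A citizen flagged under usual care goes on accruing time after the team switches, when nurses start receiving lists. If one yes/no result per citizen is assigned to the phase of the flag, admissions in that later period count against usual care. This can pull a real effect towards the null.

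The effect sought is small: 12% v 10.8%, an odds ratio of (0.108/0.892)/(0.12/0.88) = 0.89. An undefined window and crossover rule could easily outweigh it, and both could still be chosen after the data are seen.

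**Working it through.** **Plan's own figures.** The article gives no figure for follow-up by phase or for time after the switch. Its only related figure is overall power of at least 0.22 (printed as β). This does not follow from the printed inputs alone: ignoring clustering, 5,500–6,000 citizens give one-sided power of 0.40–0.43. The Hussey–Hughes stepped-wedge formula with an assumed intracluster correlation of 0.05 gives 0.22. That figure matters here only for the cost of the fix.

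**Inputs from the article.** Teams: 10, 7 and 3. Step lengths: 4, 6 and 12 weeks (Odense, Svendborg, Kerteminde). Period: 52 weeks. Population aged over 65 (Table 1), used as weights: 35,811, 14,206 and 6,142.

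**Assumptions.** First flags are uniform over the 52 weeks. The first team crosses at week 0 or after one interval (the figure is not shown). Follow-up ends at week 52, or at week 65 with three months added. There is no censoring at admission, death or relocation.

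**Step 1: share of control-flag follow-up after the switch.** For a team switching at week T with follow-up to week E, control-phase time is proportional to T²/2 and total time to E·T − T²/2. The share is 1 − Σ(T²/2) / Σ(E·T − T²/2).

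Odense, first switch after one interval, E = 52: T = 4, 8, …, 40, ΣT = 220, ΣT² = 6,160. Control-phase time is 3,080 and total time is 52 × 220 − 3,080 = 8,360. The share is 1 − 3,080/8,360 = 63%.

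| All three municipalities, weighted | First switch after one interval | First switch at week 0 |
|---|---|---|
| End at week 52 | 62% | 68% |
| End at week 65 | 72% | 76% |

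Equal team weights give the same range within a point. With every first flag at week 0, the range is 56–69%.

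**Step 2: mean follow-up to week 52.** In the Odense example, control flags have 8,360/220 = 38.0 weeks. Intervention flags have Σ(52 − T)²/2 divided by Σ(52 − T) = 5,160/300 = 17.2 weeks. Over all municipalities and both start rules: 38–39 v 17–19 weeks.

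**Step 3: result with no true effect and no time adjustment.** The article attaches no period to its 12%. Taking 12% per 90 days as an assumption, the hazard is −ln(0.88)/(90/7) = 0.0099 per week, and the chance of any admission is the average of 1 − exp(−0.0099 × follow-up).

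- End at week 52: 31–32% v 15–17%, odds ratio 0.39–0.43.
- End at week 65: 39–40% v 25–27%, odds ratio 0.52–0.54.
- If the 12% is taken per 30 days or per year instead, the odds ratio ranges from 0.29 to 0.60 over the same scenarios.

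**Step 4: if a window of w weeks was intended.** The share of control windows crossing the switch is Σmin(T, w)/ΣT. Odense, 30 days (w = 4.29), first switch after one interval: (4 + 9 × 4.29)/220 = 19%.

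| Window from flag | Control windows crossing the switch | Control follow-up after the switch |
|---|---|---|
| 30 days | 19–21% | 9–11% |
| 90 days | 51–57% | 27–30% |

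**The case against.** The strongest reply is that silence about an end is not a statement that follow-up is open-ended. The article condenses a fuller protocol, and the one- and three-month follow-up may be the intended horizon. That stands as far as it goes: a reader might infer that most control follow-up is certainly spent under the intervention, and the article does not support this. With a 30- or 90-day window the post-switch share is about 10% or 30%. But the table gives windows to other outcomes and none to the primary one, and a crossover rule is needed under any of these windows.

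Second, the Discussion promises adjustment for time, and the analysis follows the randomization schedule with repeated-measures methods. A reader might infer from Step 3 that the trial will report a spurious odds ratio near 0.4. It need not: that is the unadjusted worst case. Splitting follow-up at the switch may even be intended, but the text does not say so, and a single yes/no per citizen does not do it.

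Third, time after the team's switch is not all treated time. Nurses assess only citizens who are still, or again, on the list. A reader might infer that a real effect shrinks to a fraction of its size. No dilution was calculated, and it depends on how many control-flagged citizens are flagged again.

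Fourth, share of follow-up is not share of events. Under the constant hazard in Step 3 and an end at week 52, 58–65% of first admissions among control flags fall after the switch. If risk is assumed to peak at the flag (three times baseline, six-week decay), this falls to 48–53%. So for events, "most" is not secure even on the open-ended reading.

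**Conclusion.** The point holds in a conditional form. The primary outcome lacks an end, and no rule covers a citizen flagged before the team's switch and admitted after it. The primary comparison is therefore not defined, which goes beyond omitted detail.

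On the open-ended reading with uniform first flags, control flags have about twice the follow-up of intervention flags, and 62–68% of it (72–76% with three months added) lies after the switch. Without time adjustment the null odds ratio would be about 0.4–0.5 at 12% per 90 days. Time adjustment may reduce that bias, but it does not take post-switch time out of the control outcome, and the resulting dilution is real in direction but unknown in size. On a 30- or 90-day reading the contamination is much smaller but still touches about a fifth or a half of control windows.

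Confidence is high on the two omissions. The size of the consequences depends on the stated assumptions.

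**What to change.** Define the primary outcome as acute admission (yes/no) per flagged citizen within one fixed window, of equal length in both phases, counted from the first flag. Thirty days is one example, since the article already uses that horizon; the choice of length is for the investigators. Set exposure by the team's scheduled phase in each week, so that follow-up is split at the switch. A discrete-time logistic model on person-weeks with calendar time included would do this. Apply the same rule to 90-day death. State that the denominator is flagged citizens.

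The cost is mainly wording, because weekly algorithm data and register admissions are already collected. The real downside is that fewer admissions count than with open-ended follow-up, in a trial whose stated overall power is only about 0.22. The power figure should be restated for the chosen window.
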